| To assess the diagnostic performance of KK2.0 in comparison to KK1.0 at detecting hookworms ( Necator americanus and Ancylostoma duodenale ) and Ascaris lumbricoides and Trichuris trichiura in SAC living in selected areas of Ucayali, a remote Amazonian region of Peru, at the 30-minute and 24-hour timepoints, respectively, of slide preparation. | 
 
Eggs per gram (EPG)
 
Sensitivity of KK1.0 and KK2.0 at 30-minute and 24-hour timepoints
 
Agreement in KK1.0 and KK2.0 results at 30-minute and 24-hour timepoints
 
Percentages of SAC with low, moderate, or heavy intensity of infection by EPG
 
 |
| Secondary                                                                                                                                                                                                                                                                                                                                                                      |                                                                                                                                                                                                                                                                                                                            |
| To evaluate the prevalence STH (hookworms [ Necator americanus and Ancylostoma duodenale ], and Ascaris lumbricoides and Trichuris trichiura ) in the selected endemic, remote Amazonian region of Ucayali, Peru.                                                                                                                                         | 
 
STH prevalence as a percentage in SAC living in the selected areas of Ucayali, Peru
 
                                                                                                                                                                                      |

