Within 1 hour of stool sample arriving at the laboratory site, lab technicians will prepare from each sample a TSET assay, and 2 KK thick-smear slides (differentiated as Slide A and Slide B; see [Figure 1](#) for schematic flow chart and Peru KK2.0 Laboratory Protocol for a narrative description). One technician will prepare the sample for TSET and count the number of *A. lumbricoides*, *T. trichiura*, hookworm eggs, and any other additional identifiable parasites. This will provide qualitative data for later analysis. Two other lab technicians, using the same homogenized stool sample, will prepare the 2 KK thick-smear slides, Slide A and Slide B. Slides A and B will be analyzed within the first 30 minutes ( $\pm 10$  minutes) of slide preparation, in order to count hookworm eggs. Hookworm eggs will clear (ie, eggs will hatch) and disappear from stool samples within this window of time. Slide A will be analyzed via the KK1.0 method that uses manual counts of *A. lumbricoides*, *T. trichiura*, hookworm eggs, and any other identifiable parasites in the 30-minutes timeframe, and Slide B via the KK2.0 method that uses automated egg counts. Slide B will be loaded into the AI-DP slide scanner (aka KK2.0 method) and the system will automatically collect images of the slide. An on-board AI program will process the images, identifying eggs for verification. The slide images and identified eggs will be later uploaded to a cloud database and subsequently uploaded to the study database. See KK2.0 AID2STOP User Manual.

Slide B will be refrigerated overnight to allow the sample to become clearer from sediment and debris so that *A. lumbricoides* and *T. trichiura* eggs can be more easily identified. At the  $24\pm 4$ -hour timepoint, Slide B will undergo a manual (KK1.0) and digital (KK2.0) egg count. Slides will be randomly selected for the KK1.0 method first or KK2.0 method second, or vice versa.

All slides read by the KK1.0 method will be converted to eggs per gram (EPG) of stool statistics and uploaded to the study database. The images of all slides scanned into the AI-DP tool will be uploaded to the EggInspector application (see EggInspector Quick Start Guide) in the cloud database which will identify the eggs and the images will be validated by an expert parasitologist in Peru. Validated results will be uploaded to the study database.

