Following data collection and upload to the study database, data will undergo quality control, cleaning, and eventually database lock. Ten percent of all slides (ie, KK1.0 and TSET) and 100% of KK2.0 will undergo quality control at each timepoint, where they will be recounted for eggs at the end of the day.

All positively identified specimens for parasites as well as those with negative results by TSET will be summarized at the central laboratory, as per the standard of care in Peru. A signed letterhead by the laboratory's director will be delivered to the children's parents/guardians by the field workers notifying them of their children's infection status (Visit 4) with the recommendation to follow up with their healthcare provider clinic for treatment if positive for any STH or other parasites.

The collection of stool samples will be conducted for approximately 3 months followed by a 2-month period for analysis of results.

The different steps of the trials are schematized in Figure 1.

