**QC (10 % at Random)****Day 1**

**Sedimentation (00 Hrs) [+ (2-5)/ ++ (6-10) / +++ (> 10)] (MARK only: 1, 2 or 3)**

\* Hookworm= Ancylostoma/Necator

[figure not shown]

Negative  
Yes

|   |                            |   |                            |   |                            |   |                            |   |                            |   |                            |          |                            |   |                            |   |                            |    |                            |
|---|----------------------------|---|----------------------------|---|----------------------------|---|----------------------------|---|----------------------------|---|----------------------------|----------|----------------------------|---|----------------------------|---|----------------------------|----|----------------------------|
| 1 | Ascari
s                | 2 | Trichuris                  | 3 | Hookwor
m *             | 4 | E.
vermicu
laris     | 5 | H.
nana                 | 6 | H.
diminut
a         | 7        | Taenia                     | 8 | Fasciol
a               | 9 | S.
stercoral
is      | 10 | Giardia                    |
|   |  + |   |  + |   |  + |   |  + |   |  + |   |  + |          |  + |   |  + |   |  + |    |  + |
| 1 | Capilla
ria sp          | 1 | D.
pacificum            | 1 | Trichostro
ngylus       | 1 |                            | 1 |                            | 1 |                            | Comments |                            |   |                            |   |                            |    |                            |
|   |  + |   |  + |   |  + |   |  + |   |  + |   |  + |          |                            |   |                            |   |                            |    |                            |

**SLIDE A - KK1.0 (30 + - 10 min)  
(All Parasites Egg N°)**

| Factor |   |   |
|--------|---|---|
| 8      | 1 | 2 |
|        | 2 | 4 |

| Stool
TYP
E |
|-------------------|
|                   |

1= Normal, formed  
(24)  
2 = Pasty (12)  
3= NO N- LIQUID  

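### Hookworm timing: the end-of-day manual recount and the 24-hour primary results do not fit the protocol's own account of how early hookworm eggs clear

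*Protocol*

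**What the plan says.** All of this is in the protocol; the Synopsis repeats the Section 3.1.1, objectives and main analysis text in much the same terms.

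- **Early read (Section 3.1.1).** "Slides A and B will be analyzed within the first 30 minutes", with a 10-minute tolerance, so that hookworm can be counted. The reason given is: "Hookworm eggs will clear (ie, eggs will hatch) and disappear from stool samples within this window of time".
- **Overnight step (Section 3.1.1).** Slide B is kept cold until 24±4 hours so that Ascaris and Trichuris "eggs can be more easily identified". Hookworm is not named as a reason for this read.
- **QC rule (Section 3.1.1).** The manual share is "Ten percent of all slides (ie, KK1.0 and TSET"). The same sentence sets the digital share and the timing that applies to both: "100% of KK2.0 will undergo quality control at each timepoint, where they will be recounted for eggs at the end of the day". No species is excepted, and the text does not say whether the digital recount uses the slide or its image.
- **QC form (Attachment 1).** The part headed "QC (10 % at Random") repeats, under Day 1, a block headed "SLIDE A - KK1.0 (30 + - 10 min") with a hookworm field.
- **Primary objective (Section 2).** It lists hookworm, then Ascaris and Trichuris, to be assessed "at the 30-minute and 24-hour timepoints, respectively, of slide preparation". The endpoints beside it give sensitivity and agreement at both times, with no limit by species.
- **Analysis (Section 4.3.1).** N(+) for each species is the union of the four Kato-Katz reads and TSET. A positive by any method at any time counts as true. Results are ordered by method, species and timepoint, and the sensitivity formula extends to the other methods and times. The 24-hour manual form in Attachment 1 has a hookworm field.

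**The concern.** Two sets of statements do not fit together.

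The first concerns QC. If hookworm eggs are being lost around the 30-minute read, a manual recount of the same smear hours later does not measure the same thing. A lower second count could mean that the first reader over-counted, that the second reader missed eggs, or that the eggs had gone. A form that labels the late recount as a 30-minute reading hides the difference from whoever analyses it. This is the only repeat read of manual hookworm counts that the protocol describes.

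The second concerns the primary results. The objective and the stated purpose of the overnight step both place hookworm at 30 minutes. The endpoint list and Section 4.3.1 nevertheless produce 24-hour hookworm EPG, sensitivity, intensity and agreement with the same standing as the rest. Both methods would then be compared on a smear from which most hookworm eggs are expected to be missing. Section 4.3.1 urges caution about the 30-minute comparison because two different slides are read. That could lead a reader to prefer the same-slide 24-hour comparison, which for hookworm is the less informative one.

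**Working it through.** The protocol states no power, error rate or expected agreement, so there is no figure of its own to reproduce. The check is a comparison of texts, with two counts and one illustration.

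**1. Size of the manual QC sample.** Inputs: 500 children (Section 4.1), one Slide A each and a 10% fraction (Section 3.1.1, Attachment 1). 0.10 × 500 = 50 Slide A recounts. Hookworm prevalence is not given. At assumed values of 5%, 10% and 20%, about 50 × 0.05 = 2.5, 50 × 0.10 = 5 and 50 × 0.20 = 10 of these recounts come from infected children.

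**2. Timing of that recount.** The form's window closes at 30 + 10 = 40 minutes. Section 4.2 has 12 Slide Bs read per day, so a similar number of samples presumably arrives daily, and for most of them the end of the day falls well after 40 minutes. One recount cannot meet both the text and the form's label. The first-minus-second difference is reader disagreement plus loss by clearing, and one late recount cannot separate the two.

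**3. Digital QC.** Images are captured at the read, stored and later validated (Section 3.1.1). A recount of 30-minute images sees the same eggs whenever it is done. A recount of the physical Slide B meets the problem in step 2.

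**4. Primary comparisons.** 3 species × 2 times = 6. The clearing statement undercuts one: hookworm at 24 hours. Let r be the share of hookworm-positive samples whose Slide B still shows eggs at 24 hours. Apart from false positives, neither method's 24-hour sensitivity can exceed r, because both read that slide. The protocol gives no r.

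**5. N(+).** Because N(+) is a union, a 24-hour negative never removes an earlier positive. Only false 24-hour positives can distort it. As an illustration, assume complete clearing, D infected children and two independent 24-hour reads, each with false-positive rate f:

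- extra positives = (500 − D) × [1 − (1 − f)²]
- ceiling on 30-minute sensitivity = D / (D + extra)

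For D = 50 and f = 1%: 450 × (1 − 0.9801) = 450 × 0.0199 = 8.96, and 50 / 58.96 = 0.848.

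| Assumed prevalence (D) | f = 0 | f = 0.5% | f = 1% | f = 2% |
|---|---|---|---|---|
| 5% (25) | 100% | 84% | 73% | 57% |
| 10% (50) | 100% | 92% | 85% | 74% |
| 20% (100) | 100% | 96% | 93% | 86% |

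Both prevalence and f are assumptions. With f = 0 the reference is unaffected. If the two reads share their false positives, fewer are added.

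**The case against.** The strongest reply is that the clearing sentence explains why the first read must be early and does not claim total loss. Taken literally, loss within the window would empty the 30-minute read as well. That stands, and it rules out several stronger conclusions that a reader might draw:

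- **That hookworm recounts will be near zero and QC agreement will fall to 0%.** This needs complete clearing by the end of the day, which the protocol does not state.
- **That about 10% of manual hookworm positives will be lost.** This needs a rule that recounts replace first reads. There is none, and Attachment 1 gives QC its own fields, which suggests separate recording.
- **That the whole digital QC is invalid.** Stored 30-minute images can be recounted without loss.
- **That 24-hour hookworm reads corrupt the reference.** If both methods read close to zero, the union hardly changes. Harm needs false positives.
- **That 24-hour hookworm agreement will look falsely high.** Raw agreement might, but the planned weighted kappa is corrected for chance. With almost all reads negative it would be unstable or undefined.

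It is also fair that the study is descriptive with no prespecified hypotheses, so no error rate is at stake, and that showing hookworm at 24 hours is legitimate description. QC detail may be in the laboratory protocol cited in Section 3.1.1 or in Figure 1, neither of which is at hand.

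The two contradictions remain. The protocol itself fixes the recount time, the form's label, N(+) and the endpoint times. A later analysis plan could restrict the tables, but it cannot recover eggs lost before a recount.

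**Conclusion.** The point holds as two internal inconsistencies of moderate weight.

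First, about 50 of 500 Slide A reads are due a late recount whose hookworm result cannot be read as a measure of reader error. This rests on clearing continuing after the window, which is the evident sense of Section 3.1.1, and not on every egg being gone. Digital QC shares the problem only if slides are recounted.

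Second, one of six species-by-timepoint primary comparisons, hookworm at 24 hours, conflicts with the objective and is expected to tell little about either method. The effect on N(+) is conditional. It is nil without false 24-hour hookworm positives. Under the assumed rates of 0.5% to 2% per read at 10% prevalence, it would cap 30-minute sensitivity at 92% to 74%. If many genuine hookworm eggs do survive to 24 hours, the clearing statement in Section 3.1.1 is what needs correcting. Either way the sections must be reconciled.

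**What to change.** - **Manual QC.** Reconcile Section 3.1.1 with the QC form. Exclude hookworm from the end-of-day Slide A recount, or do that recount inside the window on the form where existing staff can. The protocol gives no reading times or spare capacity, so a second full read within the window cannot be assumed to be free.
- **Digital QC.** State that hookworm QC uses the stored 30-minute images.
- **Primary analysis.** Carry the objective's wording into the endpoints and Section 4.3.1: hookworm compared at 30 minutes, Ascaris and Trichuris at 24 hours, with 24-hour hookworm results supportive only.
- **Reference.** Define a hookworm N(+) from KK1.0 at 30 minutes, KK2.0 at 30 minutes and TSET, as the main or a sensitivity reference.

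The analysis and reference changes need wording only and no new reads. The downsides are that manual hookworm counts lose their late recount unless it can be done in time, and that any genuine residual 24-hour hookworm positives leave the reference if the reduced N(+) is made the main one. The primary hookworm comparison also stays a comparison of two slides, so the caution in Section 4.3.1 still applies to it.

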**Figure 1: Stool Sample Collection and Analysis for Soil-transmitted Helminthiasis in the Jungle Region of Ucayali, Peru**

[figure not shown]

Abbreviations: AI=artificial intelligence, EPG=eggs per gram, KK=Kato Katz

Further details are provided in Section 3.2 and Section 3.3, respectively.

Prior to data collection, all children and/or their legally acceptable representative where applicable must sign a participation informed/assent consent form (ICF) allowing data collection and source data verification in accordance with local requirements and/or sponsor policy.

The end of the study will be the last stool sample collected within the study for the last participating child. The overall duration of the study, including recruitment, is expected to be approximately 7 months followed by a 2-month period for analysis of results. The stool sample collection is expected to be completed within 3 of those 7 months.

The expected frequency and timing of data collection in this non-interventional study are summarized in the [DATA COLLECTION SCHEDULE](#) presented after the synopsis.

### **3.1.2. Rationale for Study Design**

This prospective, non-interventional field study design is an effective way of collecting data in STH endemic regions to evaluate an improved STH diagnostic tool (AI-DP) over the standard approaches to allow for a more accurate and efficient data collection, with the aim of promoting a more targeted use of STH drug donations. The incorporation of this tool into STH monitoring programs in STH endemic countries, such as in the Ucayali region of Peru, will help to overcome the diagnostic issues of accessibility, affordability and quality, thus ensuring that data reporting is fully integrated into national health data systems for more efficient and precise targeted drug donations.

### **3.2. Study Setting**

There will be no formal study sites in this study. Trained local field workers will visit houses in areas A, B, C, D, E, and F as indicated in the map of Ucayali, Peru and will obtain approximately 500 fresh stool sample from consented and assented participating SAC. Samples will be collected and taken to the laboratory for analyses.

### **3.3. Patient Population**

School-aged children in selected STH endemic areas of Ucayali, a remote Amazonian region of Peru is the target patient population in this study. The study will focus on SAC (age 5–14) since they have a higher burden of STH infection and are a major target of PC programs for treating STH. An informed consent will be obtained from parents of SAC, aged 5-14 years, and an additional assent will be obtained from SAC older than 8 years. All SAC in a household encounter by the field worker will be asked to provide a fresh stool sample.

#### **3.3.1. Patient Selection Criteria**

All children who meet the selection criteria below will be encouraged to participate by the field workers.

Each field worker will assess children to determine their eligibility for sample collection within the study based on the selection criteria. If there is a question about any of the selection criteria,

the field worker should consult with the appropriate sponsor representative before enrolling the child.

**Inclusion Criteria**

Each potential child participant must satisfy the following criteria to be eligible for data collection in this study:

1. Male or female aged 5 to 14 years of age, inclusive, as this group is at high risk for STH morbidity [13]
2. Child is otherwise in healthy condition as stated by their parents
3. Parent(s)/guardian(s) of children must sign, and/or their legally acceptable representative where applicable must sign, a ICF indicating that they understand the purpose and procedures required for the study and that they are willing to have their child participate in the study
4. Child of 8 years or older has signed an assent document indicating that they understand the purpose of the study and procedures required for the study, and are willing to participate in the study
5. Child is able to provide an adequate stool sample as specified on stool collection container
6. Parent/Guardian and child speak Spanish

**Exclusion Criteria**

Potential child participant who meets any of the following criteria will not be eligible for this study:

1. Child has active diarrhea (defined as the passage of 3 or more loose or liquid stools per day) at baseline
2. Child has an acute medical condition or is experiencing a severe concurrent medical condition
3. Child has received anthelmintic treatment within 90 days prior to study entry

**3.3.2. Participating Patient Completion/Withdrawal**

Data collection will be considered complete for a participating child if data collected has been recorded in the electronic case report form (eCRF).

A child participant will be withdrawn from data collection within the study for any of the following reasons:

- Withdrawal of consent
- Decision by the sponsor during the study (eg, due to major protocol violation, including failure to meet the study selection criteria)
- Liquid diarrhea on the day of sample collection

### 3.4. Data Sources and Data Collection Methods

The [DATA COLLECTION SCHEDULE](#) that follows the synopsis summarizes the expected frequency and timing of children contact in this non-interventional study, which must be in accordance with clinical practice, and subsequent data collection.

The primary data sources for this study will be the Demographic Data Collection Form ([Attachment 2](#)) and the Sample Processing Form ([Attachment 1](#)). Demographic information of each child will be collected at their home (Visit 2) by the field worker and recorded on the Demographic Data Collection Form. Stool sample analyses will be done at the laboratory and data will be recorded on the Sample Processing Form by the lab technician. All data will be entered in the eCRF by the lab coordinator, who is an expert lab technician.

Where available, the following items are to be documented at baseline:

- Demographic data
- Collection of stool sample
- Measures of effectiveness/clinical response (see Section [3.4.2](#))

#### 3.4.1. Soil-transmitted Helminthiasis Therapy

This study will consist of a stool specimen collection and baseline data collection and no therapy will be investigated.

#### 3.4.2. Measures of Effectiveness/Clinical Response

##### 3.4.2.1. Effectiveness/Clinical Response Measures

At the laboratory, trained laboratory technicians will prepare stool-thick-smear slides for KK1.0, KK2.0, and stool concentrations for the TSET method and will be read manually and by the KK2.0 method at specific timepoints and in accordance with standard process for each test. Slide images read by the AI-DP tool will be uploaded to the EggInspector application in the cloud database (see EggInspector Quick Start Guide), then manually verified by an expert parasitologist in Peru. Validated results will be uploaded to the study database.

Definitions of appropriate measures of effectiveness/clinical response are as follows:

- KK1.0 method: The microscopy diagnostic standard for diagnosing STH infection intensity. Stool samples are made into a slide smear in which eggs are counted.
- KK2.0 method: An improved diagnostic technique over KK1.0 in development that uses AI-DP technology to facilitate egg counting without using a microscope. Using the KK thick

smear technique, stool slide smear will be inserted into a slide scanner to provide an automated egg count. At present, this is a hybrid methodology that uses AI-DP and an expert parasitologist verification.

- TSET method: A qualitative method commonly used in LATAM to monitor for STH infection using a concentration by sedimentation assay, without centrifugation.
- Positive to any STH result: Any sample with egg(s) of any STH species identified by any of the diagnostic methods.

